### Identification of Participants and Consent

As this is an evaluation study of a voluntary training program offered to GP practices as part of the usual program of NHS Health Improvement training, individual consent will not be required. By logging in to the Internet-based training website, practices will be agreeing to participate in the evaluation of the effectiveness of the training. No practices, staff, or patients will be identified during the evaluation. This information is in the letter instructing practices how to log into the training website. Patient data will be used to evaluate the outcomes of the training program, but this will be at the level of the intervention (ie, by GP practice) using health record linkage. The patient data and practice ID will be anonymized and accessed via the NHS Greater Glasgow and Clyde IT Safe Haven, so no individual patient consent will be sought.

All practices will be informed about the available training via communications from clinical directors and other routine NHS communication sources, which will explain the purpose of STBD and provide contact details to use if they are interested in completing the training. Those practices that do opt in will be randomized to one of the two arms of the evaluation. Practices gaining immediate access to the Internet-based training will be emailed with instructions on how to access the site (Arm 1). They will also be sent a practice kit containing the print materials designed to support implementation of STBD within their practice. Those practices randomized to Arm 1 will be sent options for the supplementary face-to-face training sessions and instructions on how to book a place through NHS Greater Glasgow and Clyde Health Improvement. Practices that express an interest and are randomized to Arm 2 (ie, delayed access to the STBD training), will be notified by email that their instructions for access will be available in 4 months. They will be made aware that their referral data over the next 4 months will be analyzed as part of the evaluation. A reminder letter/email/ phone call will be sent/made to any practice that opts in and does not access or complete the Internet-based training module after 4 weeks.

It will be made clear within correspondence with practices that completion of the training is entirely voluntary and that data for referrals, weight management, and diabetes outcomes will be examined to evaluate the impact of the new Internet-based training, but neither individual practitioners nor practices will be identified in any output.

### Trial Schedule

The schedule and timeline for the trial are outlined in Table 2.

**Table 2 table2:** Trial schedule and timeline.

Activity	Owner	Outcome	Estimated timeline
Ad placed within primary care communication channels and forums	University of Glasgow and NHS^a^ Greater Glasgow and Clyde	Notify practice of training. Opt-in of practices to evaluation	Oct 2017
Randomization	University of Glasgow	Randomized practices that opt in to Arm 1 or 2 using Castor Electronic Data Capture	Oct 2017-Apr 2018
Practices notified of arm for evaluation	University of Glasgow	Practices informed if they are immediate or delayed access to training by email	Oct 2017-Apr 2018
Arm 1: Practices sent patient materials, posters, and invited to complete Internet-based training with or without face-to-face training	NHS Greater Glasgow and Clyde Health Improvement	Practices randomized to Arm 1 or 2 invited to complete training	Oct 2017-May 2018
Notification of completion of Internet-based training (Arm 1)	University of Glasgow	Website analytics notifies research team of Internet-based training completion by practice code	Oct 2017-Sept 2018
Reminder notice/phone call	University of Glasgow	Practices not having completed the Internet-based training will be sent a reminder and also the practice will be phoned once	Nov 2017-May 2018
Provision of face-to-face training (Arm 1)	NHS Greater Glasgow and Clyde Health Improvement	Notification of attendees provided to NHS team	A study-specific face-to-face training session available every 2 months Oct 2017-Jun 2018
Access to referral data	NHS Safe Haven	Statistician has remote access to anonymized data via a virtual private network	Oct 2018
Comparison of change in referral rate (Arms 1 vs 2)	Statistician	Report of results	Dec 2018

^a^NHS: National Health Service.

### Randomization

Practices will be randomized to immediate or delayed intervention using the Internet-based random allocation software (Castor Electronic Data Capture) using permuted random block sizes of 4.

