**Methods:**

We used the Behavior Change Wheel to develop an intervention for staff in primary care consisting of a 1-hour Internet-based eLearning package covering the links between obesity, type 2 diabetes, and the benefits of weight management, the treatment of diabetes in patients with obesity, specific training in raising the issue of weight, local services and referral pathways, overview of weight management components/ evidence base, and the role of the referrer. The package also includes a patient pamphlet, a discussion tool, a practice implementation checklist, and an optional 2.5-hour face-to-face training session. We have randomly assigned 100 practices in a 1:1 ratio to either have immediate access to all the resources or have access delayed for 4 months. An intention-to-treat statistical analysis will be performed.

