### Trial Design

A randomized trial design will be used for this evaluation with GP practices randomly assigned to one of the two arms described. We will notify clinicians of the STBD package and evaluation through primary care management, training forums, and communications. If interested, the practices will be able to opt in to the STBD evaluation via email. Once a practice has expressed interest, they will then be randomized to one of the two arms and either receive immediate access to the Internet-based training and print materials or receive access 4 months later (with awareness that their referral rates will be monitored).

The inclusion criteria for participants requires that they be GP practices in NHS Greater Glasgow and Clyde that have a contract for local enhanced services for long-term conditions (ie, diabetes) and have a unique clinical database (ie, not shared with another practice). Practices classified as “17c” (those with a separate NHS contract for long-term conditions) and those practices with a database shared with another practice (8 practices in area) are excluded.

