### Statistics

Comparisons between study arms will be by independent two-sample *t* tests or appropriate nonparametric equivalents using the prespecified comparisons.

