### Data Handling

We have prepared a custom electronic case report form for the purposes of randomizing the practices to immediate or delayed access to STBD training at the point of opting in. The remaining data for use in this evaluation will be from routine health records (ie, weight management and diabetes care). Access to these data will be via the NHS Greater Glasgow and Clyde Safe Haven (already approved by the Local Privacy Advisory Committee). The data will be fully anonymized and accessed via a virtual private network. Access will be only for the duration of the analysis of the data for the evaluation.

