## Results

The first invitations for this evaluation were emailed in October 2017. Recruitment for this trial closed in April 2018. As there was an extremely large response to the single invitation email from the Primary Care Diabetes Lead sent in March 2018, to avoid discouraging willing practices we decided to extend the trial to include 100 practices (50 per arm). Follow-up is ongoing and linkage of practice data with referral data was completed by October 2018. It is expected that the trial will report in early 2019.

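### A single fixed block size of 4 in an open trial that randomises practices as they opt in makes one third of assignments deducible in advance by anyone who knows the size and tracks past assignments

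*Protocol article*

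**What the plan says.** All references are to the protocol article.

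- **Randomization:** allocation is by internet-based software, "using permuted random block sizes of 4". No second size and no stratification factor is named.
- **Abstract, Methods:** "We have randomly assigned 100 practices in a 1:1 ratio".
- **Trial Design:** "Once a practice has expressed interest, they will then be randomized to one of the two arms". **Data Handling** adds that the electronic form serves for "randomizing the practices to immediate or delayed access to STBD training at the point of opting in".
- **Trial Schedule, Table 2:** the University of Glasgow owns the randomisation step ("Randomized practices that opt in to Arm 1 or 2 using Castor Electronic Data Capture") and also the notification step ("Practices informed if they are immediate or delayed access to training by email"), both from October 2017 to April 2018.
- **Results:** recruitment closed in April 2018, after an "extremely large response to the single invitation email from the Primary Care Diabetes Lead" in March.
- **Statistics:** "Comparisons between study arms will be by independent two-sample" t tests or nonparametric equivalents.

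**The concern.** Neither practices nor the notifying institution can be blinded to immediate versus delayed access, so concealment of the next assignment is the main protection against selection at entry. Central software hides the list. It does not hide what follows by deduction from earlier assignments once the block size is known. With one small fixed size that deduction is often exact.

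Someone who knew the next arm could choose which practice to enter next, or when to enter it. The primary outcome is a before/after referral ratio, which depends on the baseline level, so selective ordering could in principle make the arms differ at entry. The sentence also attaches the word random to the block sizes, which may lead a reader to credit the design with varied sizes.

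**Working it through.** The article gives no predictability figure to reproduce, so this is a direct enumeration.

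**Inputs.** Block size 4 (Randomization). Ratio 1:1 and 100 practices (Abstract), hence 100/4 = 25 complete blocks. Sequential entry (Trial Design, Data Handling). A single list is inferred because no strata are named; with strata the fraction per completed block would be the same.

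**Assumption.** The observer knows the block size and the full order of past assignments.

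**Step 1: possible orders.** A 1:1 block of 4 has 4!/(2!·2!) = 6 orders: AABB, ABAB, ABBA, BAAB, BABA, BBAA. That is 6 × 4 = 24 assignments.

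**Step 2: certain assignments.** The fourth is always determined (6 of 6). The third is determined when the first two match (AABB and BBAA, 2 of 6). The first and second never are. Total 6 + 2 = 8, and 8/24 = 33.3%. Over 25 blocks: 25 × 4/3 ≈ 33 of 100 practices.

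**Step 3: best guess (always name the arm with more places left).**
- Position 1: 1/2.
- Position 2: 2/3.
- Position 3: 1/3 × 1 + 2/3 × 1/2 = 2/3.
- Position 4: 1.

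Mean = (1/2 + 2/3 + 2/3 + 1)/4 = 17/24 = 70.8%, against 50% with full concealment.

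**Step 4: alternatives.** Fixed sizes are enumerated exactly. Varied sizes are simulated (100 allocations, 2,000 runs, sizes equally likely, observer knows the set of sizes but not the draws).

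| Block sizes | Known with certainty | Best guess correct |
|---|---|---|
| 4 fixed | 33.3% | 70.8% |
| 6 fixed | 25.0% | 68.3% |
| 8 fixed | 20.0% | 66.6% |
| 4/6 varied | 5.6% | 69.2% |
| 4/6/8 varied | 2.2% | 67.9% |
| 2/4/6 varied | 4.2% | 70.1% |

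Varying the size removes nearly all certainty but little of the guessing advantage. On the scale 2p − 1, fixed 4 gives 2 × 0.708 − 1 = 0.42 and 4/6/8 gives 2 × 0.679 − 1 = 0.36.

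**Step 5: what a retrospective check could detect.** Each arm of 50 would have about 50/3 ≈ 17 practices in predictable positions and 33 in others. The difference detectable with 80% power at two-sided 5% is about 2.80 × √(1/17 + 1/33) = 0.84 SD, or roughly 0.85 SD with a t test. Only a gross imbalance would show.

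**The case against.** The strongest reply is that foreknowledge needs something to act on, and the article shows little.

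- Practices volunteer by email and eligibility is objective, so no recruiter judges suitability. This stands, and it narrows the exposure to the order and timing of entry.
- Table 2 names institutions, not people. It does not show that the same staff entered practices, sent the emails and knew the block size. This also stands; a condensed article may leave separation of roles to the full protocol.
- A reader might infer from the large March 2018 response that practices waited in a queue whose order could be chosen. The Results section reports a response, not a queue or a choice of order. Entry in order of receipt, or as one batch, would leave little or no room for steering.
- A reader might infer that staff could see which practices were low or high referrers, because the five feasibility practices spanned a range of referral rates. That does not extend to the 100 volunteers. Table 2 gives referral data to the statistician, anonymised, in October 2018, after recruitment closed.
- A reader might want a bias figure. Suppose the better of two waiting practices is chosen at every certain slot, with a correlation r of 0.2 to 0.3 between visible promise and outcome and the protocol's hypothetical SD of 1.12. Then (1/3) × 2 × 0.564 × r × 1.12 gives 0.08 to 0.13. Apart from the SD, none of these behavioural inputs has a source in the article, so this is a scenario and not an estimate.
- A reader might infer that October-to-April entry lets season bias the comparison. Blocks filled in time order keep the arms balanced over calendar time, so ignoring period costs at most precision. A full analysis plan may add covariates, so the brief Statistics section is not itself at fault.

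None of this removes the structural point: the stated rule makes a third of assignments deducible, and a near-costless alternative existed.

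**Conclusion.** The point holds as a weakness in a stated design rule and as loose wording. For an observer at the responsible institution who knew the size and tracked the sequence, 8/24 of assignments (about 33 of 100) were certain in advance and 17/24 could be guessed correctly. These figures rest on a single fixed size of 4, 1:1 allocation, complete blocks and that observer's knowledge.

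The documents do not show that the foreknowledge was used, that a queue existed, or that randomising staff knew practices' referral rates. They do not support a claim that allocation was compromised, and no size of bias can be derived from them.

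**What to change.** **Change to the plan as designed.** Use randomly varying block sizes, for example 4, 6 and 8, not disclosed to the staff who enter practices. Alternatively, where many practices respond together, enter the whole list before any assignment is revealed and randomise it as one batch. The cost is a setting in the allocation system and one sentence. The drawback of varied sizes is that the arms may end a few practices apart: an unfinished block of 8 can leave a gap of at most 4.

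**What remains possible now that recruitment has closed.**

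1. Reword the Randomization section to say that a single fixed block size of 4 was used, and state the resulting predictability as a limitation. If responders were entered in order of receipt or in batches, say so, since that would lessen the concern.
2. Include randomisation period (for example before or after the March 2018 email) as a factor in the primary comparison. This turns the t test into a linear model with arm and period. The purpose is precision; it does not remove selection bias.
3. Optionally, compare baseline referrals within arm between predictable and other positions. Report this as a descriptive check only, because its power is low and a null result would not be reassuring.

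Item 1 costs a few sentences. Items 2 and 3 need the randomisation date or order carried through the anonymised linkage, plus one covariate and one table.

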### Outcome Measures

The primary outcome is change in primary care referral rate to an adult NHS weight management service. Using data from the weight management database held by NHS Greater Glasgow and Clyde, the ratio of referrals over 3 months before and after the STBD intervention (allowing 1 month for completion) will be calculated. Secondary outcome measures include change in referral, including uptake ratio, local enhanced service template completion (weight management discussed); change in local enhanced service template completion; completion of lifestyle weight management phase (completion defined as 80% attendance); weight change (kg and %) in lifestyle weight management phase for those attending >1 session; and weight change (kg and %) at 1 year for all patients (data from annual diabetes review). Tertiary outcomes include diabetes medications at time of referral, that is percentage on weight gaining medications (sulphonylureas, thiazolidinediones, insulin), and percentage on weight neutral/reducing medications (GLP-1 agonists, metformin, DPP-IV inhibitors, SGLT2 inhibitors). Exploratory analyses (before and after) will be carried out to look at the effect of completion of training; change in referral rate analysis of those who completed Internet-based training only; when training done was completed by GP only, by practice nurse only or both; and change in referral rate in those where one practice member completed Internet-based plus face-to-face training.

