## Introduction

Scottish Intercollegiate Guideline Network guidance recommends that “obese adults with type 2 diabetes should be offered individualized interventions to encourage weight loss (including lifestyle, pharmacological or surgical interventions) in order to improve metabolic control” [1]. Despite the existing recommendations, provision of weight management services is currently patchy around the United Kingdom [2,3]. Where services are available, high attrition rates are often reported [4]. In addition, individuals often fail to take up services even after having seemingly agreed to do so. That is, after discussion with a general practitioner (GP) or practice nurse, individuals are referred to the service but do not attend for an appointment [5].

In the National Health Service (NHS) Greater Glasgow and Clyde Health Board area of Scotland, there are currently 25,109 patients with type 2 diabetes and a body mass index (BMI) ≥30 kg/m^2^, yet only 5855 patients with type 2 diabetes were referred to Glasgow and Clyde Weight Management Service from 2005-2014. Of those, only 1537 attended at the assessment session and only 336 completed the program and lost at least 5 kg [4].

The Glasgow and Clyde Weight Management Service delivers a specialist multidisciplinary, multicomponent, weight management program throughout the Glasgow and Clyde area of the United Kingdom. In an evaluation of the service, the authors highlighted that 27% of the patients who are referred to the program do not opt into the service [6]. This describes patients who are referred via their GP practice and do not contact the service to opt into an initial assessment. Similarly, Brook et al [7] described initial uptake and engagement of a small weight management program of 502 patients. In addition to completing an extensive questionnaire, patients were requested to call to make an appointment with the service personally**.** Of those referred to the program, 46% did not opt in. Engaging patients in a weight management program is especially difficult, even when the intervention is provided via the primary care route. For example, the Counterweight Project, a weight management program delivered via a GP practice, has been taken up by several practices in Scotland. However, after 2 years, one fifth of enlisted practices failed to enroll patients into the program [8].

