### Sample Size

A feasibility study was completed during which five practices (from a range of current referral rates to weight management services and deprivation areas in NHS Greater Glasgow and Clyde) were provided with access to the STBD e-learning program in June 2016. A GP and practice nurse from each attended a 2.5-hour face-to-face training session, and the practices were provided with the implementation toolkit. The referral rate to uptake was assessed for the 3 months prior to the STBD training (March-May 2016), 3 months post- STBD training (October-December 2016), and the same 3 months in 2015 (October-December 2015). We saw an increase in referrals of 50% compared to same period the year before (n=8 and 15 referrals respectively) and 88% compared to previous 3 months (n=10 and 15 referrals respectively) after the STBD intervention. Two practices did not make any referrals in the immediate time period analyzed prior to the intervention. As a result of this, together with the small number of feasibility practices, it was difficult to make a formal power calculation. The effect compared to same period 12 months before was 1.5 (SD 1.21); effect compared to 3 months previous was 1.88 (SD 0.38). A sample size of 80 per group would give 80% power to detect a difference of 0.5 in the change in referral rate based on a hypothetical SD of 1.12.

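### The primary outcome, a practice-level referral ratio, has no value for practices with no baseline referrals (2 of 5 in the pilot), so as defined it cannot cover all randomised practices and it costs power

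*Protocol article*

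**What the plan says.** Under Outcome Measures, the protocol article first labels the endpoint: "The primary outcome is change in primary care referral rate to an adult NHS weight management service". The only calculation it then gives is that "the ratio of referrals over 3 months before and after the STBD intervention (allowing 1 month for completion) will be calculated". The PICOS summary in the Introduction repeats the ratio. The Statistics section compares arms by independent two-sample t tests "or appropriate nonparametric equivalents using the prespecified comparisons". The Abstract (Methods) promises: "An intention-to-treat statistical analysis will be performed".

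The Sample Size section describes the pilot ("A feasibility study was completed during which five practices") and reports: "Two practices did not make any referrals in the immediate time period analyzed prior to the intervention". It says that this, together with the small number of practices, made a formal power calculation difficult. It then gives 80 per group for 80% power to detect a difference of 0.5 with a hypothetical SD of 1.12. The Results section states that 100 practices, 50 per arm, were included. The article gives no rule for a zero denominator and no allowance in the sample size for practices without a ratio.

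**The concern.** A two-sample test needs one number per practice. Referrals after divided by referrals before has no value when the earlier count is zero. The pilot met this problem and the outcome was kept. Three commitments then conflict: the ratio as endpoint, a test on practice-level values, and inclusion of every randomised practice.

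An untreated zero baseline leads either to dropped practices or to a handling choice made once the data are in hand. Dropping them removes practices that did not refer at all, although low referral is the problem that the protocol sets out to solve (Intervention Development, Step 1). It also reduces the usable number in a trial that already has 50 rather than 80 per arm. Among the remaining practices, a ratio of small counts is noisy, and it weights a practice with one baseline referral the same as one with many.

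**Working it through.** **Inputs.** Difference 0.5, SD 1.12, 80 per group and 80% power (Sample Size); 50 per arm (Results); 2 of 5 pilot practices with zero baseline; 10 pilot referrals in the previous three months as printed, a mean of 10/5 = 2.0 per practice. Alpha is not stated; two-sided 0.05 is assumed. The printed text reads "88% compared to previous 3 months (n=10 and 15 referrals respectively", but 15/10 = 1.50 and 15/8 = 1.88. The two pairs of counts may be transposed, in which case the mean is 8/5 = 1.6.

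**Step 1: reproduce the stated size.** n = 2(1.96 + 0.84)² × (1.12/0.5)² ≈ 79 per group by the normal approximation, and 80 by the exact noncentral t (power 80.1%). The stated 80 reproduces, on the premise that every practice supplies a ratio.

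**Step 2: share of undefined ratios.**
- Pilot: 2/5 = 40%, exact 95% CI 5% to 85%.
- Low scenario: if all practices shared a Poisson mean of 2, exp(−2) = 13.5%.

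**Step 3: power with the protocol's own inputs (noncentral t).**

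| Share undefined | Usable per arm, of 50 | Power |
|---|---|---|
| 0% | 50 | 60% |
| 13.5% | 50 × 0.865 ≈ 43 | 53% |
| 40% | 50 × 0.60 = 30 | 40% |

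Keeping 80 usable per arm at a 40% loss would need 80/0.60 ≈ 134 per arm.

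**Step 4: is the ratio itself inefficient?** Simulation with 50 per arm, mean 2 referrals per practice per window and true rate ratio 1.5. Counts were Poisson, with gamma variation between practices and, in some runs, extra variation within a practice between windows. The ratio t test drops zero-baseline practices. The count model is a quasi-Poisson regression of the post-window count on arm and log(pre-window count + 0.5), using all practices.

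| Zero-baseline share | Ratio t test | Count model, all practices |
|---|---|---|
| 39-41% | 23-34% | 41-62% |
| 14% | 56% | 86% |

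At 39-41% zeros, the lower figure in each cell comes from runs with extra within-practice variation. A t test on the pre-post difference, also defined for every practice, had about 59-63% power near 40% zeros without that extra variation and 34% with it. At 13.5% zeros it had 65%.

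**Step 5: does a simple patch rescue the ratio?** A t test on (post + 0.5)/(pre + 0.5) keeps every practice but had only about 26-30% power. Ranking could place practices with post > 0 and pre = 0 at the top. However, 0/0 remains undefined without a further convention, and about 26-28% of practices fell there in the overdispersed runs.

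**The case against.** Zero handling is often left to an analysis plan, and none is shown here. The article allows nonparametric alternatives and refers to prespecified comparisons. It never says that zero-baseline practices will be dropped, and its label, change in referral rate, could also cover a difference. This stands as far as it goes: exclusion is one consequence of the printed definition, not a stated rule. But the article itself fixes the ratio and the type of test while reporting the zero denominators. The add-a-constant patch does not recover the lost power, and a rank test still needs a convention for 0/0.

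Four stronger readings are tempting, and the documents do not support them.

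- **The between-arm comparison would be biased.** Provided that the baseline window precedes allocation, excluding on that count should not distort the contrast. In simulation, type I error of the t test after exclusion was 4-6%. The harm is to power, to the population described and to the intention-to-treat claim.
- **More than half of practices would have zero baseline.** A reader might take the Introduction's figure ("only 5855 patients with type 2 diabetes were referred to Glasgow and Clyde Weight Management Service from 2005-2014") and compute 5855/(10 × 4 × 260) = 0.56 per practice per quarter. That spreads old area-wide data evenly over all practices and conflicts with the pilot mean of about 2, so it is not used.
- **The ratios all rest on counts of one to three.** As printed, ten baseline referrals came from three practices, so at least one had four or more.
- **The ratio explains the whole power deficit.** The fall from 80% to 60% comes from 50 rather than 80 per arm and is a separate issue.

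The t test as such is not the main fault, since a t test on the pre-post difference beats the ratio. The 40% share is also imprecise, but the count model's advantage remains at 14% zeros.

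**Conclusion.** The concern holds for the ratio as defined. It gives no value for zero-baseline practices and so cannot meet the intention-to-treat statement without a further rule. On the protocol's difference and SD, the power lost at 50 per arm is about 7 points (60% to 53%) if 14% of ratios are undefined and about 20 points (60% to 40%) if 40% are. The simulated gap to a count model on all practices is about 18 to 30 points.

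These sizes rest on two-sided alpha of 0.05, the hypothetical SD of 1.12, a pilot mean near 2, a true rate ratio of 1.5 and gamma-Poisson counts. The share of undefined ratios is known only from five practices. That the ratio is undefined at zero depends on none of these assumptions.

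**What to change.** Before arms are compared, replace the primary analysis with one defined for all 100 randomised practices. The preferred form is an overdispersed Poisson or negative binomial regression of the post-window referral count on arm and log(pre-window count + 0.5), reporting the between-arm rate ratio with 95% CI. Take the p-value from a permutation test of the arm label that respects the blocks of four, because quasi-Poisson type I error reached about 7% in some runs. A t test on the pre-post difference in counts is an acceptable simpler alternative. Keep the raw ratio as a descriptive summary, stating how many practices have none.

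The cost is a change of analysis wording and a few lines of code, with no new data. The effect scale changes, so the 0.5 target must be re-expressed; it corresponds to a rate ratio of about 1.5 only if the control arm's ratio is 1.

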Given the importance of weight management for type 2 diabetes, we sought to develop and evaluate an intervention to improve referral rates and uptake of weight management programs for patients with type 2 diabetes and co-existent obesity (Textbox 1).

PICOS summary.ParticipantsPrimary care practices in National Health Service Greater Glasgow and Clyde, United Kingdom (at least 1 clinician per practice)InterventionA 1-hour eLearning program covering the benefits of weight management in type 2 diabetes, communication skills for raising the issue of weight with patients, and safe management of diabetes during weight loss; patient information pamphlets; patients discussion aid; an implementation toolkitComparatorPrimary care practices that did not get access to the interventionOutcomesPrimary – the ratio of referrals over 3 months before and after the Small Talk Big Difference intervention (allowing 1 month for completion)Secondary – change in referral: uptake ratio; local enhanced service template completion (weight management discussed); change in local enhanced service template completion; completion of lifestyle weight management phase (completion defined as 80% attendance); weight change (kg and %) in lifestyle weight management phase for those attending >1 session; weight change (kg and %) at 1 year for all patients (data from annual diabetes review)Tertiary – diabetes medications at time of referral: % on weight gaining medications (sulphonylureas, thiazolidinediones, insulin); % on weight neutral/reducing medications (GLP-1 agonists, metformin, DPP-IV inhibitors, SGLT2 inhibitors)Exploratory – the effect of completion of training; change in referral rate analysis of those who completed Internet-based training only; when training done was completed by GP only, by practice nurse only or both; change in referral rate in those where one practice member completed Internet-based plus face-to-face trainingStudy DesignIndividually randomized controlled trial

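### Template completion is listed as both a level and a change and compared without baseline adjustment; one baseline-adjusted comparison would be more precise and give one answer

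*Protocol article*

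**What the plan says.** The Outcome Measures section of the protocol article gives, within its list of secondary outcomes, "local enhanced service template completion (weight management discussed); change in local enhanced service template completion; completion of lifestyle weight management phase". The PICOS summary in the Introduction repeats the pair as two items separated by a semicolon: "local enhanced service template completion (weight management discussed); change in local enhanced service template completion". Neither place says which of the two answers the question.

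The Statistics section is a single sentence covering all comparisons between arms: "Comparisons between study arms will be by independent two-sample *t* tests or appropriate nonparametric equivalents using the prespecified comparisons". It names no baseline covariate for any outcome.

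The Results section reports that the trial was extended to 100 practices, 50 per arm. Template completion has no stated SD, expected effect or pre-post correlation.

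**The concern.** The intervention aims to get clinicians to raise weight with patients who have type 2 diabetes, and to do so more often (Step 3 of Intervention Development). Of the listed outcomes, template completion is the closest record of that behaviour. Listing it as both a level and a change asks one question twice. If only one of the two comparisons shows a difference, the article gives the reader no way to tell whether discussion of weight improved.

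Precision is also lost. The level comparison ignores the pre-period value. The change comparison subtracts it in full, which is too much unless the pre-post correlation is 1. Because a change cannot be calculated without the pre-period value, the covariate for a better single analysis is already in hand.

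**Working it through.** **Inputs from the article.** 50 practices per arm (Results). Unadjusted two-sample comparison (Statistics).

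**Alpha.** The article states none, so I recovered it from the Sample Size section: "A sample size of 80 per group would give 80% power". The difference assumed there is 0.5 and the SD is 1.12. The normal formula gives n = 2 × (1.96 + 0.842)² × (1.12/0.5)² = 2 × 7.85 × 5.02 ≈ 78.8, hence 79 per group. The t-based solution is 79.7, hence 80, which is the stated figure. One-sided 0.05 would give 63. The implied level is therefore two-sided 0.05. That figure concerns the primary outcome, and I use it here only to fix alpha.

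**Assumptions, not in the article.** Equal SD before and after (set to 1), approximate normality, change taken as a simple difference, pre-post correlation r of 0.3, 0.5 or 0.7, and an illustrative effect of 0.5 SD.

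**Variance of the arm difference, relative to the level comparison.**
- Level: 1
- Change: 1 + 1 - 2r = 2(1-r)
- Baseline-adjusted (ANCOVA): 1-r²

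Adjusted against level: 1 - (1-r²) = r², which is positive unless r = 0. Adjusted against change: 2(1-r) - (1-r²) = (1-r)², which is positive unless r = 1. The adjusted comparison is therefore more precise than both for every r strictly between 0 and 1.

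**Power.** The standard error of the level difference is √(2/50) = 0.2, so the expected z is 0.5/0.2 = 2.5. For relative variance V, power ≈ Φ(2.5/√V - 1.96).

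| r | V: level / change / adjusted | expected z | power |
|---|---|---|---|
| 0.3 | 1 / 1.40 / 0.91 | 2.50 / 2.11 / 2.62 | 0.70 / 0.56 / 0.75 |
| 0.5 | 1 / 1.00 / 0.75 | 2.50 / 2.50 / 2.89 | 0.70 / 0.70 / 0.82 |
| 0.7 | 1 / 0.60 / 0.51 | 2.50 / 3.23 / 3.50 | 0.70 / 0.90 / 0.94 |

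In terms of practices at r = 0.5, an unadjusted comparison in either form would need 50/0.75 ≈ 67 per arm to match the adjusted one with 50.

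**Disagreement.** The two test statistics have correlation (1-r)/√(2(1-r)) = √((1-r)/2), which is 0.59, 0.50 and 0.39 at r = 0.3, 0.5 and 0.7. If both were tested at two-sided 0.05 and the true effect were 0.5 SD, the bivariate normal gives a probability of 0.30, 0.28 and 0.28 that exactly one is significant.

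**The case against.** The strongest reply is that the flaw is small. Both comparisons are unbiased under randomisation, the outcome is secondary, and referral change is the single primary. Against the better of the two unadjusted forms, the gain in power is about 4 points at r = 0.3, 12 at r = 0.5 and 4 at r = 0.7. It vanishes as r approaches 0 (against level) or 1 (against change). Neither r nor the 0.5 SD effect comes from the article. All of this stands and limits the weight of the point, but it does not make either unadjusted form the better choice.

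It can also be said that the two entries may not be the same measure. The bracketed qualifier about weight management being discussed follows only the first entry, and neither entry has a stated denominator or window. The second could mean completion of the whole template. Duplication is the likelier reading, but it remains a reading.

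A reader might infer more: that each entry is tested at full alpha, that the false-positive rate is therefore inflated, and that the whole secondary list lacks multiplicity control. The article does not support this. It states no alpha, does not say that every listed item receives a hypothesis test, and refers to prespecified comparisons that it does not list. An analysis plan that is not shown may set a ranking or make one form descriptive.

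A reader might also see the same doubling in the weight outcomes. There, the lifestyle-phase result covers patients who attended more than one session, while the 1-year result covers all patients. These are different populations and questions, and kg and % are two units for one result.

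**Conclusion.** The point holds in a limited form. The article lists level and change of template completion side by side in two places and fixes an unadjusted method for comparing arms, although the change outcome presupposes a pre-period value. Neither form is biased, but they can disagree. Each is less precise than one adjusted comparison for any r strictly between 0 and 1. The ordering of variances follows from algebra, given equal SDs and change taken as a difference. The power figures (about 0.82 against 0.70 at r = 0.5) also depend on the assumed effect, the normal approximation, two-sided 0.05 and 50 practices per arm. The primary outcome is not affected. The point is worth acting on because the better analysis costs almost nothing, not because the present one is invalid.

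**What to change.** In the PICOS summary and in Outcome Measures, replace the two template entries with one secondary outcome: the practice's post-period template completion proportion. In Statistics, state that it is compared between arms with adjustment for the same practice's pre-period proportion, by ANCOVA on practice-level proportions or by a binomial model with practice-level overdispersion. Report one arm difference with its 95% CI, and show raw level and raw change by arm descriptively. If the second entry was meant as a different measure, say so and define it.

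The cost is a regression in place of a t test; no new data are needed. Timing needs care. The Trial Schedule puts data access in October 2018 and the arm comparison in December 2018, Results says linkage was completed by October 2018, and the article appeared in February 2019. If the data have already been accessed, date the change and declare it as made after access.
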